### Interventions

#### PTSD treatment

All patients in the project will receive PTSD treatment at one of six outpatient clinics in the MHS-CRD that provides PTSD treatment. All clinics comply with official Danish recommendations for PTSD Care Packet-treatment (CP-treatment) [22]. PTSD CP-treatment consists of 60 h trauma-focused group psychotherapy or 15 h trauma-focused individual therapy combined with other treatment elements such as assessment, psychoeducation, pharmacological counselling/treatment, social skill training, meeting with social network, and monitoring. The CP includes 75 h of treatment in total (Table 1).

**Table 1 Tab1:** Care package treatment for post-traumatic stress disorders

CP content	hours
Psychiatric and somatic assessment	3 h
Psychometry (monitoring) and psychoeducation	2 h
Group psychotherapy	60 h
Psychopharmacology	2 h
Social skills training and couple counselling	4 h
Continuity and coherence in ongoing treatment	4 h
Total	75 h

#### PTSD help

The *PTSD help* app is designed for use in preparation for and as a supplement to psychotherapy. The app includes a range of different functions. It contains psychoeducation about PTSD on a range of different topics including PTSD symptoms, etiology, prognosis, treatment, trauma in general, and information for next of kin on how to offer support to individuals suffering from PTSD. The app contains tools for self-assessment and monitoring of PTSD symptoms (*PTSD checklist for DSM-5,* [53]) and sleep quality (*Sleep Condition Indicator*, [25]). For alleviating sleep problems, the app has two different audio-recorded guided meditations and advice for improving sleep habits and sleep environment. It also contains different tools and techniques for relieving anxiety such as distraction exercises, a breathing exercise with an animated prompt to help the user regulate his or her breath, physical relaxation and simple yoga exercises, calming images accompanied with music, and an option for taking personal notes on the experience of specific symptoms and helpful strategies to reduce distress associated with these symptoms. And finally, it has a crisis plan with personal contacts and contact information for psychiatric emergency services. The features selected for the app were chosen based on advice from resident clinical experts and empirical evidence drawn primarily from the cognitive behavioral tradition of psychoeducation and anxiety management training [28, 29] and from cognitive behavioral treatment for insomnia [11, 51]. In addition, some features based on yoga and meditation practices were included, based on emerging evidence for their potential effectiveness [30, 36]. *PTSD help* was freely available to participants in the experimental group, but is currently not broadly available for download. The current build of the app will be kept stable throughout the intervention.

### Assessment interview

The patient’s trauma history is assessed with *The Trauma History Questionaire* [31], a 24-item self-report measure of the patient’s lifetime trauma history. PTSD diagnosis and comorbid disorders are assessed through the *Mini International Neuropsychiatric Interview* (MINI v. 7.02) [50], a structured diagnostic interview that assesses the presence of psychiatric disorders according to DSM-5. To ascertain whether the patient also fulfills the criteria for *International Classification of diseases 11*^*th*^*revision pending* (ICD-11) PTSD or C-PTSD, the *International Trauma Questionaire* (ITQ) [19] is administered. ITQ is a 23-item self-report questionnaire used to distinguish between PTSD and C-PTSD as defined in ICD-11.

### Feasibility outcome

The primary feasibility outcome is the proportion of eligible patients that agree to be randomized and participate in assessment 1 (T1, week 1) and 2 (T2, week 7). The secondary feasibility outcome is the fraction of compliant patients in the experimental group that is patients that actively use the system after. Compliance is defined as the use of *PTSD help* functions (excluding self-monitoring tools) corresponding to use twice a week (mean), assessed over 6 weeks pre-treatment, and during the psychotherapy treatment period. Compliance data is collected from the tracking log of the patient’s app activity through a secured webpage. In addition, compliance will be assessed through a *user behaviour questionnaire,* an 11-item questionnaire developed by the project group for the current study by selecting and modifying relevant items from questionnaires used in earlier studies evaluating the *PTSD Coach* app [34, 44] (see Additional file 1).

### Exploratory outcomes

Exploratory outcomes in the study are app intervention dropout rate, psychotherapy dropout rate, and a range of patient outcome variables measured with the following questionnaires (Table 2). PTSD symptoms are measured using the *PTSD Checklist for DSM-5* (PCL-5) [53], a 20-item self-report questionnaire that assesses the presence of the four core DSM-5 PTSD symptom clusters during the past month. The *Dissociative Symptoms Scale* (DSS) [12] is used to measure the presence of dissociative symptoms. DSS is a 20-item self-report questionnaire measuring four domains of dissociation: depersonalization, derealization, gaps in awareness or memory, and dissociative re-experiencing. The patient’s general level of psychological distress is measured with *the Symptom Checklist-10* (SCL-10) [3], a 10-item measure of general psychological distress, derived from the *Symptom Checklist-90* (SCL-90). SCL-10 is composed of questions that measure the three factors of the SCL-90 that accounts for the largest amount of variance: depression, somatization, and phobic anxiety. *WHO-5* [2] is used to measure the patients’ quality of life. WHO-5 is a 5-item self-report questionnaire that measures well-being during the last 2 weeks. Patient sleep quality is measured with the *Sleep Condition Indicator* (SCI) [25, 37], an 8-item questionnaire. The patient’s readiness to change is measured with *The University of Rhode Island Change Assessment Short version* (URICA-S) [41], a short version of the URICA self-report questionnaire [42]. URICA-S is a 16-item measure. Possible negative effects of the *PTSD help* intervention are measured with the *Negative Events and Results of Psychological Treatment–Revised* (NEQ-rev) [31, 49], a 13-item self-report questionnaire that aims to assess negative effects associated with psychotherapeutic interventions, e.g., suicidal thoughts, lower self-esteem, increased stress level, and worsening of symptoms. NEQ-rev is a revised version of NEQ. All items in NEQ that directly concern treatment-related conditions or outcomes of psychotherapy are excluded (see Additional file 2 for a list of excluded items), as the patients do not undergo psychotherapeutic treatment at the time NEQ-R is administered. To measure user experiences, *the user satisfaction questionnaire* was developed by the project group. This is a 17-item self-report questionnaire that assesses the patient’s perceived benefit from using the app *PTSD help*. The project group developed the questionnaire selecting, translating, and modifying relevant items from two questionnaires used for evaluation of the *PTSD Coach* app by Kuhn et al. [33] and Miner et al. [44] (see Additional file 1).

**Table 2 Tab2:**
[figure not shown]
SPIRIT figure

*T1* enrollment, baseline assesment, and randomization, *T2* post-primary app intervention 6 weeks after baseline, *T3* end of psychotherapy treatment, *MINI* Mini**-**International Neuropsychiatric Interview**,***THQ* Trauma History Questionnaire, *I* International Trauma Questionnaire, *PCL-5* PTSD Checklist for DSM-5, *SCI* Sleep Condition Indicator, *DSS* Dissociative Symptoms Scale, *WHO-5* WHO-Five Well-being Index, *SCL-10* Symptom Checklist-10, *URICA-S* University of Rhode Island Change Assessment Scale-Short, *NEQ* Negative Effects Questionnaire, *Feasibility and Acceptability Questionnaires* developed specifically for this project by the research team

^a^Revised version of NEQ, 13 questions selected

### Adverse events

As the interventions included in the app does not include any trauma-focused interventions or other symptom provoking interventions, we do not expect any adverse effect from use of the app. However, to ascertain whether this assumption is correct, we include the *Negative Events and Results of Psychological Treatment–Revised* to measure possible adverse effects.

### Statistical analysis

The primary and secondary outcomes are analyzed through descriptive statistics, e.g., percentage of patients that show up at T2, the average usage of the system over the intervention period, and the proportion of patients that stay in study until the end.

Analysis of between-group effects on explorative outcome measures will be analyzed with analysis of covariance, using the intervention arm as the main predictor and baseline severity and the stratification variable from randomization as covariates. For binary outcomes (e.g., compliance), logistic regression will be used. Due to the exploratory nature of this feasibility study, missing data will not be imputed but the amount of missingness will be reported. Results will be presented as covariate adjusted group differences or odds ratios, along with the 95% confidence interval. If the results indicate feasibility, we will proceed to a randomized controlled efficacy study.

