### Randomization

Randomization is conducted through the data management software REDCap, which allows a setup where no one from the research team has knowledge of or access to the underlying computer-generated allocation sequence. The randomization uses permuted blocks with varying block sizes based on a computer-generated allocation sequence created by a researcher with no affiliation to the project. The randomization allocation ratio is 1:1. This procedure ensures that researchers are blinded to the allocation process as the randomization allocation list, and block size is unknown to the researchers. The randomization procedure will be stratified by presence of Complex PTSD as measured with the International Trauma Questionnaire [18].

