### Sample size

Due to a shortage of similar studies, it is not currently possible to conduct a calculation of optimal sample size for this study. Based on existing knowledge about feasibility study methodology [6, 52, 54] and two feasibility studies of mHealth tool in public health settings [9, 26], we plan to recruit 70 patients. With 70 patients, the 95% confidence interval for a proportion estimate such as compliance would range between 0.38 and 0.62 (if the observed proportion is 0.50), which we consider acceptable for planning further studies.

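### About 35 app patients cannot confirm that the app has no adverse effect, and the outputs named for exploratory outcomes do not suit rare individual harms

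*Protocol article*

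**What the plan says.** The Adverse events section of the protocol article states the expectation: "we do not expect any adverse effect from use of the app". It then gives the purpose of the harm measure: "However, to ascertain whether this assumption is correct, we include the" NEQ-rev. The sentence closes by saying that the instrument measures possible adverse effects.

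The Exploratory outcomes section places NEQ-rev among the exploratory outcomes. It is a 13-item self-report whose content is illustrated by "e.g., suicidal thoughts, lower self-esteem, increased stress level, and worsening of symptoms".

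The Statistical analysis section assigns the exploratory outcomes as follows: "Analysis of between-group effects on explorative outcome measures will be analyzed with analysis of covariance, using the intervention arm as the main predictor", with baseline severity and the stratification variable as covariates. Binary outcomes go to logistic regression. Missing data are not imputed, but their amount is reported. The output is fixed: "Results will be presented as covariate adjusted group differences or odds ratios, along with the 95% confidence interval". Plain descriptive statistics are assigned to the primary and secondary outcomes.

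The sample follows from "we plan to recruit 70 patients" (Sample size) and "The randomization allocation ratio is 1:1" (Randomization). The number per arm is not stated; 70/2 = 35 is derived.

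**The concern.** The article sets out to establish that an assumption of no harm is correct, and NEQ-rev is the only instrument it names for that purpose. Two parts of the plan do not match this aim.

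- **Size.** An absence of events in a small group is weak evidence of an absence of risk. The Discussion itself says that the small sample rules out testing clinical effects on the outcome measures, yet the Adverse events section asks the same sample to settle the question of harm.
- **Form of the result.** For content such as suicidal thoughts, what matters is how many patients reported it. An adjusted mean difference or an odds ratio does not answer that when events are few.

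At stake is the safety statement that accompanies the app into a larger trial. A finding of no difference in negative effects could be taken as support for the assumption when the data do not give that support.

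**Working it through.** **Inputs.** From the article: 70 patients, 1:1 allocation, 13 items, 95% intervals. Derived: 35 per arm. Assumed, because the article gives no figure: number of responders, number of events, scoring of NEQ-rev, and its SD.

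**The plan's own figure.** The Sample size section says that "the 95% confidence interval for a proportion estimate such as compliance would range between 0.38 and 0.62" at an observed 0.50. Check: 0.50 ± 1.96 × √(0.5 × 0.5/70) = 0.383 to 0.617. It reproduces. It describes a proportion near one half in all 70 patients, not a rare event in one arm.

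**Zero events in the app arm.** The exact two-sided 95% upper limit for 0 of n is 1 − 0.025^(1/n).

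| App patients answering | Upper limit |
|---|---|
| 35 (all) | 10.0% |
| 28 (assumed) | 12.3% |
| 26 (assumed) | 13.2% |
| 21 (assumed) | 16.1% |

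The one-sided limit for n = 35 is 1 − 0.05^(1/35) = 8.2%. If the true rate were 5%, zero events in 35 would still occur with probability 0.95^35 = 17%. To exclude 5% with zero events at the two-sided level takes ln(0.025)/ln(0.95), rounded up to 72 exposed patients, which is more than the whole planned trial.

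**Non-responders.** With 26 of 35 responding and no events observed, the proportion over all randomised app patients lies between 0/35 and 9/35 = 26%.

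**If NEQ-rev is analysed as a score.** Suppose it is a count of endorsed items, and 3 of 35 app patients but no controls report suicidal thoughts. The app-arm mean rises by 3/35 = 0.09 items. The unadjusted 95% half-width of the arm difference is 1.99 × SD × √(2/35) = 0.476 × SD, so 0.95 items for SD 2 and 1.43 items for SD 3. It would fall below the shift only if the SD were under 0.086/0.476 = 0.18 items. Covariate adjustment would narrow the interval somewhat, but not to that extent under these SDs.

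**If an item is analysed as binary.** With 3/35 against 0/35 the odds ratio is (3 × 35)/(32 × 0), which has no finite value. With 0/35 against 0/35 it is undefined. Ordinary logistic regression therefore gives no usable estimate in either case. The two counts remain fully informative.

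**The case against.** The strongest reply is that the article does not fix how NEQ-rev is analysed. It does not say whether the items are summed, whether they are tabulated singly, or which arm answers them; the assessment schedule is a figure that is not shown. Such detail is often left to a full protocol or analysis plan. The Adverse events sentence also ends on measuring possible adverse effects, and the analysis plans estimates with intervals, not a test of no harm.

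Much of this stands, and it rules out several stronger readings that a reader might infer:

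- *That harm is judged only by an ANCOVA mean difference.* The next sentence of the same section gives logistic regression for binary outcomes, so a yes/no item could be handled there.
- *That the analysis fails because NEQ-rev has no baseline of its own.* The covariate is baseline severity, which could be a symptom scale measured at T1.
- *That patients who stop using the app drop out of the harm data.* Nothing restricts the emailed questionnaires to continuing users, and missingness is to be reported.
- *That a null NEQ-rev result would trigger the efficacy trial.* That step is tied to feasibility.

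Two things survive. The stated purpose of checking that the assumption is correct is in the text and exceeds the sample. And both output forms that the text does name serve rare harms poorly, whichever one NEQ-rev is given.

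**Conclusion.** The point holds as a limited and inexpensive improvement. With about 35 app patients, the trial can describe negative effects but cannot confirm their absence: zero events is compatible with a true rate of up to 10.0%, and up to 12.3% to 16.1% with 28 down to 21 responders. This rests on equal arms of 35 and an exact two-sided 95% limit; the responder numbers are assumptions.

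The point about the form of the result is conditional. Dilution applies if NEQ-rev is scored as a mean or sum, and its illustrated size depends on an assumed count score and an SD of 2 to 3 items. The empty-cell problem applies if items are treated as binary. The documents do not show that item counts are excluded, only that they are not among the outputs named for exploratory outcomes.

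**What to change.** **Adverse events section.** Replace the aim of ascertaining that the assumption is correct with the aim of describing reported negative effects. Add that zero events among about 35 app patients excludes only rates above about 10%, and that the limit rises with non-response.

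**Statistical analysis section.** State that NEQ-rev is reported as the number of patients endorsing each item, in each arm that receives it, with suicidal thoughts and worsening of symptoms shown separately. Give exact 95% intervals among responders, the number of non-responders, and best/worst-case bounds over all randomised patients in the arm (none, or all, of the non-responders counted as events).

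**Optional.** Tabulate by arm the proportion of patients who worsen on PCL-5 and SCL-10 from T1 to T2, with the amount that counts as worsening set in advance.

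**Cost.** Two wording changes and one extra table; no new instrument, visit or patient. The downside is a weaker safety statement, which is the one the data can carry.

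### Compliance is the named example for a between-arm logistic regression, but it exists only in the app arm, so its arm odds ratio cannot be estimated

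*Protocol article*

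**What the plan says.** All references are to the protocol article.

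- **Feasibility outcome** sets the population: "The secondary feasibility outcome is the fraction of compliant patients in the experimental group". Compliance there means using app functions, self-monitoring tools excluded, at an average rate of two times per week. The source is stated: "Compliance data is collected from the tracking log of the patient’s app activity through a secured webpage".
- **Abstract (Methods)**, **Procedure** and **PTSD help** give the app to the experimental group only. The comparator is care as usual alone, and the app is not on general release.
- **Statistical analysis**, first paragraph: "The primary and secondary outcomes are analyzed through descriptive statistics".
- **Statistical analysis**, second paragraph, deals with between-group effects on the exploratory measures, "using the intervention arm as the main predictor and baseline severity and the stratification variable from randomization as covariates". It then says "For binary outcomes (e.g., compliance), logistic regression will be used", and closes the reporting rule with "Results will be presented as covariate adjusted group differences or odds ratios, along with the 95% confidence interval".
- **Exploratory outcomes** begins its list this way: "Exploratory outcomes in the study are app intervention dropout rate, psychotherapy dropout rate". Neither dropout rate is defined further.

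**The concern.** The logistic sentence sits inside a paragraph whose model has arm as its main predictor and whose output is an adjusted group difference or odds ratio. Read in place, it asks for an odds ratio of compliance between the app arm and care as usual. Compliance is a property of people who hold the app, so that contrast has no counterpart in the control arm.

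The section also disagrees with itself, because the same outcome is assigned a descriptive analysis one paragraph earlier. An analyst following the second paragraph literally would either get a failed or divergent fit, or would report an effect of having the app on using the app, which carries no information. A penalised fit would return a finite number, but for that same empty contrast.

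**Working it through.** **Inputs.** 70 patients (Sample size) and 1:1 allocation (Randomization) give about 70/2 = 35 per arm. The model terms are intercept, arm, baseline severity and the stratification variable (complex PTSD), so four columns. Missing data are not imputed (Statistical analysis). Where a compliance count is needed, 18 of 35 is used purely as an illustration; the protocol gives no expected value.

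**The plan's own figure.** Sample size gives 0.38 to 0.62 for a proportion such as compliance, observed at 0.50 with 70 patients. The Wald formula is p ± 1.96·√(p(1−p)/n):

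- n = 70: 1.96·√(0.25/70) = 0.117, so 0.383 to 0.617. The stated interval reproduces.

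**Coding A: controls have no compliance value.** Without imputation only the app arm enters the model. Arm equals 1 for everyone, so its column is identical to the intercept. The design matrix has 4 columns and rank 3, and the arm coefficient is not identified.

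**Coding B: every control is coded non-compliant.** The cells are 18/35 against 0/35.

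- Unadjusted log odds ratio = ln(18/17) − ln(0/35) = 0.06 − (−∞) = +∞.
- With covariates the outcome is the same. In a logistic fit with 35 per arm and simulated covariates, the arm coefficient never settles:

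| Iterations | Log odds ratio for arm | Standard error |
|---|---|---|
| 5 | 6.6 | 2.7 |
| 10 | 11.6 | 33 |
| 20 | 21.6 | 4,919 |
| 30 | 31.6 | about 730,000 |

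This is quasi-complete separation: the control arm holds one outcome only, while the app arm holds both. A Wald interval from such a fit is unusable. The result does not hinge on 18; any app-arm count above zero against 0/35 gives an infinite odds ratio.

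**What can be estimated.** The proportion within the app arm, n = 35 and p = 0.50:

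- Wald: 1.96·√(0.25/35) = 0.166, so 0.334 to 0.666.
- Wilson, half-width 1.96·√(0.25/35 + 1.96²/(4·35²)) / (1 + 1.96²/35) = 0.157, so 0.343 to 0.657.

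The Wald half-width is thus 0.166, not the 0.117 implied by a denominator of 70.

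**The case against.** The best defence is that compliance is already handled correctly elsewhere. Feasibility outcome defines it as a fraction of the experimental group, and the first paragraph of Statistical analysis describes it. That stands. A reader might infer that the planned analysis leaves the secondary feasibility outcome with no valid estimate; the document does not support this, because the descriptive app-arm proportion is planned and estimable.

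A second defence is that the logistic model was meant to study predictors of compliance inside the app arm. Such a model can be fitted, but the paragraph names arm as main predictor, promises group results, and states no within-arm model. If that was the intention, the text has to say so. Nor can this be left to a fuller analysis plan: the issue is what the article states, not what it omits.

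A third point concerns breadth.

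- A reader might extend the problem to user satisfaction. The article describes a 17-item questionnaire and nowhere says it is dichotomised, so the logistic sentence does not reach it.
- App-intervention dropout is affected only if it means stopping app use. If it means leaving the study during the six weeks between T1 and T2, both arms can contribute. The article does not say which.

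Finally, the trial is exploratory and no stated decision rule uses this odds ratio. A diverging model would probably be noticed. That limits the severity but does not make the sentence right.

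**Conclusion.** The concern holds in a narrow form and is minor. Statistical analysis assigns compliance two analyses, and only the descriptive one can be carried out. The between-arm odds ratio is either unidentified (rank 3 of 4) or infinite (0 of about 35 in controls). This rests on the definition of compliance by app-log use, on access to the app in one arm only, and on about 35 patients per arm; the non-estimability itself does not depend on the exact arm size.

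The descriptive estimate of compliance is sound, with a 95% interval of roughly a third to two thirds if half the app arm complies. The document does not support a claim that the feasibility conclusions, or the other exploratory analyses, are compromised. Logistic regression by arm remains appropriate for binary outcomes that both arms can have.

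**What to change.** Change about two sentences in Statistical analysis; no data collection or design change is needed.

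1. Remove compliance as the logistic example and name binary outcomes observed in both arms, such as psychotherapy dropout and completion of T2.
2. State that compliance is reported within the experimental arm as a proportion with a 95% confidence interval on about 35 patients (Wilson is a reasonable choice). The precision statement in Sample size should use the same denominator when it cites compliance.
3. Say what app-intervention dropout means. If it means stopping app use, report it in the experimental arm only, as for compliance.

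If a model of who complies is wanted, it should be stated separately as an app-arm model without an arm term. That is optional.
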